## Abstract

**Background:**

Extended follow-up of survivors of ICU treatment has shown many patients suffer long-term physical and psychological consequences that affect their health-related quality of life. The current lack of rigorous longitudinal studies means that the true prevalence of these physical and psychological problems remains undetermined.

**Methods/Design:**

The ICON (Intensive Care Outcome Network) study is a multi-centre, longitudinal study of survivors of critical illness. Patients will be recruited prior to hospital discharge from 20–30 ICUs in the UK and will be assessed at 3, 6, and 12 months following ICU discharge for health-related quality of life as measured by the Short Form-36 (SF-36) and the EuroQoL (EQ-5D); anxiety and depression as measured by the Hospital Anxiety and Depression Scale (HADS); and post traumatic stress disorder (PTSD) symptoms as measured by the PTSD Civilian Checklist (PCL-C). Postal questionnaires will be used.

**Discussion:**

The ICON study will create a valuable UK database detailing the prevalence of physical and psychological morbidity experienced by patients as they recover from critical illness. Knowledge of the prevalence of physical and psychological morbidity in ICU survivors is important because research to generate models of causality, prognosis and treatment effects is dependent on accurate determination of prevalence. The results will also inform economic modelling of the long-term burden of critical illness.

**Trial Registration:**

ISRCTN69112866

## Background

Research on the effectiveness of intensive care treatment has traditionally focused on mortality [1-3]. The cumulative 12 month mortality of survivors of ICU treatment in the UK varies between 35% and 43% [4,5]. Over the five years after an ICU admission these patients also have an excess risk of death when compared to an age and sex matched population [6]

However, apart from this excess mortality, recent research has confirmed that survivors of ICU treatment continue to experience both physical [7], and psychological problems [4,8,9] for some time after discharge from ICU [7,10]. The reported prevalence of anxiety and depressive problems in ICU survivors ranges from 12% to 43% (for anxiety) [4,11], and 10% to 30% (for depression) [4,11]. Two recent reviews estimate that 5% to 64% of intensive care patients may develop either post traumatic stress disorder (PTSD) or its associated symptoms that may endure for a number of years [12,13]. However, the studies reporting on the rates of PTSD and PTSD symptoms in ICU survivors vary considerably in their case mix, demographic variables, and method and timing of PTSD assessment [12,13]. All these factors complicate comparisons between studies and limit quantitative synthesis of their findings. As a result, the extent to which the consequences of critical illness or treatments received in the ICU contribute to the prevalence of PTSD symptoms during recovery is currently poorly understood. Thus, well-designed studies are needed to determine accurate prevalence rates of PTSD in survivors of ICU treatment.

The extended physical and psychological morbidity seen after critical illness has the potential to affect a patient's quality of life. Quality of life is determined by several factors including health status, social relationships, employment status and the well being of others. Health status measurements assess physical, physiologic and psychological states or function, and where these measurements overlap with components of quality of life is defined as 'Health-Related Quality of Life' (HRQoL) [14]. Studies assessing HRQoL after intensive care suggest that this improves over time [15,16], but is worse than before admission to ICU [16], and worse than general population norms [4,15,17]. However, the current literature assessing HRQoL among ICU survivors [1,3,14,18] has limitations. First existing UK studies tend to be small and from single centres. The two largest studies collected data on only 173 patients 12 months post-discharge [19] and 143 patients 3 months post-discharge [4]. Both these studies were conducted in single centres. Second, the existing studies reporting on HRQoL in ICU survivors have employed a wide number of different outcome measures, making synthesis of the results impossible. Third, the majority of the studies lack sufficient rigour. Heyland et al evaluated 64 studies assessing HRQoL in ICU survivors (January 1992 – July 1995). Only three studies (5%) met their pre-set methodological standards [14]. A major shortcoming was the lack of validation of the HRQoL measures. Hayes et al reached a similar conclusion in their systematic review [1]. The SF-36 and EQ-5D appear to be the strongest of the existing generic measures because they have been validated extensively in other patient populations and are straightforward to administer [1,3,18]. Both the SF-36 and the EQ-5D also have the advantage that utilities can be obtained which can be used to calculate quality-adjusted life years in conjunction with survival data [3,19,20]. Despite these recommendations the SF-36 and EQ-5D measures have yet to be used (or extensively validated) in a large, representative sample of survivors of adult, general intensive care in the UK [1,3]. Therefore, a UK multicentre study applying these outcome measures to assess longer-term HRQoL in survivors of ICU treatment is long overdue.

### Aims and objectives of the study

The ICON study aims to:

Define the longer-term outcomes of a large, representative sample of survivors of adult, general ICU care in the UK quantitatively in terms of their survival, HRQoL and psychological morbidity 3, 6 and 12 months after ICU discharge.

Compare the mortality of survivors of adult, general ICU care with age-, sex- and condition-matched populations of people who have not experienced ICU care.

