### Planned analyses

Using ICU admission as the event defining the start of follow-up, Kaplan-Meier curves will be constructed to illustrate survival. Age and sex matched control data will be requested from ONS in a 1:1 ratio with the patients in the study, and a control group Kaplan-Meier curve calculated from these data. A log-rank test will be used to determine the statistical significance of any differences noted.

It is almost certain that the ICU survivors will show a decreased longevity compared with the general population, so this initial testing will only be used to validate the study by showing similar results to previous investigations. However, as this is a non-randomised study, there are many potential sources for bias. To minimise the possibility that a difference in survival is due to confounders and not a real effect of the either illness or the ICU care, further covariate analysis will be undertaken. To determine the effects of covariates on survival, the Cox proportional hazards method will be used. The covariates included in the model will be age, sex, APACHE II predicted mortality, socio-economic status (from postcodes), geographical area (4 zones north to south based on hospital location), month of discharge, and 12 broad diagnostic categories based of the organ system involved in the acute illness. These results will be presented as a table showing the relative effects of ICU care and the covariates on survival.

The data on psychological illness (anxiety, depression and PTSD symptomatology), and quality of life will be largely descriptive and will be presented in tabular form.

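### The second aim promises condition-matched controls without ICU care, but the only mortality controls described are matched on age and sex, and the Cox model as described cannot separate ICU care from illness

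*Protocol article*

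**What the plan says.** The article has two aims. The second, under Aims and objectives of the study, is to "Compare the mortality of survivors of adult, general ICU care with age-, sex- and condition-matched populations of people who have not experienced ICU care".

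The Planned analyses section builds the comparator as follows: "Age and sex matched control data will be requested from ONS in a 1:1 ratio with the patients in the study". Kaplan-Meier curves are drawn for both groups, and "A log-rank test will be used to determine the statistical significance of any differences noted". The section identifies the controls with the public at large, "It is almost certain that the ICU survivors will show a decreased longevity compared with the general population", and for that reason "this initial testing will only be used to validate the study by showing similar results to previous investigations".

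A Cox model follows, intended to guard against a survival difference that is "due to confounders and not a real effect of the either illness or the ICU care, further covariate analysis will be undertaken". Its covariates are age, sex, APACHE II predicted mortality, socio-economic status from postcode, geographical zone from hospital location, month of discharge, and 12 organ-system categories of the acute illness. The output is to be a table that sets an effect of ICU care beside the effects of the covariates.

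Diagnosis and APACHE II data are described under Trial recruitment and baseline measurements, and the clinical data download under Data collection. Both concern ICU patients. The QALY comparison under Economic issues also uses controls matched on age and sex only.

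**The concern.** Two features define the comparator in the second aim: the same condition, and no ICU care. Neither appears in the description of the controls. The comparison that can be made is ICU survivors against the general public. The aim asks about ICU survivors against similar patients who did not go to ICU.

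The difference matters because the plan itself regards the general-population result as all but settled, and the Background already cites excess mortality over five years against an age- and sex-matched population. What the second aim would add is the condition-matched contrast, and no data source is described for it. If a coefficient labelled as ICU care is nevertheless reported, it will contain the effect of the illness that led to admission and of any pre-existing disease that is more common in patients than in controls.

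**Working it through.** The plan gives no effect size, event rate or power for the mortality comparison, so there is no figure of its own to reproduce. The check has three parts.

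**1. Aim against analysis**

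| Feature of the comparator | Second aim | Planned analyses |
|---|---|---|
| Age and sex | matched | matched, 1:1 |
| Condition | matched | not mentioned for controls |
| No ICU care | required | no exclusion mentioned |
| Population | people with the same condition | general population |

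No other section names a further source of mortality controls.

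**2. Can the Cox model supply what the matching lacks?**

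Age and sex exist for everyone, and postcode-based status could exist for controls. Hospital zone and month of discharge belong to a hospital stay and could at best be carried over from the matched patient. APACHE II and the acute-illness category are described for ICU patients only.

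Suppose controls have no acute-illness category. Each patient then has exactly one of the 12 indicators equal to 1, and each control has none, so

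ICU indicator = D1 + D2 + … + D12.

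- ICU indicator, age, sex and 12 categories make 1 + 1 + 1 + 12 = 15 columns. In a constructed data set of 1000 patients and 1000 controls the rank was 14.
- Adding APACHE II, set to 0 in controls, makes 16 columns. The rank was 15.

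One column is redundant in each case, so the ICU coefficient is not identified. Dropping one category as reference makes the model fit, but the ICU coefficient then measures ICU care plus the reference illness against no illness. If the model is instead fitted in ICU patients alone, nobody is unexposed and there is no ICU-care contrast. On neither reading does the model give an effect of ICU care apart from illness.

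**3. How large could the mixture be? (Illustration; every input is assumed.)**

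Let p1 and p0 be the prevalence of serious chronic disease in survivors and controls, and HR its mortality hazard ratio, with no true effect of ICU survivorship. To a close approximation,

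apparent hazard ratio = [1 + p1(HR − 1)] / [1 + p0(HR − 1)].

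- p1 = 0.3, p0 = 0.1, HR = 2: 1.3 / 1.1 = 1.18
- p1 = 0.4, p0 = 0.1, HR = 3: 1.8 / 1.2 = 1.50
- p1 = 0.5, p0 = 0.1, HR = 4: 2.5 / 1.3 = 1.92

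Simulated Cox fits used a more extreme assumption: the condition in all survivors and in 5% or 20% of controls, 12-month mortality of 5% without it, 1000 per group, and 60 runs per scenario. With no true ICU effect, the apparent hazard ratios were 1.37 to 1.48 for a condition hazard ratio of 1.5, 1.70 to 1.88 for 2, and 2.21 to 2.66 for 3. The two sets of inputs give different sizes but the same direction.

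**The case against.** Several points on the other side are fair.

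- **The unadjusted test is not offered as evidence about ICU care.** The plan limits it to validation. A reader might infer that the log-rank result will be presented as an ICU effect, and the text does not support that.
- **The authors see the mixture.** The covariate analysis speaks of an effect of illness or ICU care together. A reader who stops before those words might conclude that underlying disease is simply to be read as an ICU effect. That is too strong. What remains is that the results table is to show ICU care as an effect of its own, and no means of isolating it is described.
- **This is a condensed article.** It shows that no condition data are described for controls. It does not show that none will exist, so it would go too far to say that the comparison can never be made. But the article is not silent on the controls: it names the source, the ratio and the matching variables, and these disagree with the aim.
- **Confounding need not be complete.** Calling disease fully confounded with ICU exposure would contradict the illustration above, where 10% of controls also have the disease. The exact redundancy applies only to the acute-illness categories. Chronic disease is better described as not adjustable with the data described.
- **Controls with past ICU care** would, if anything, dilute the contrast and would not create a false ICU effect.
- **The first aim is untouched.** The study's emphasis is on psychological outcomes, those data are largely descriptive, and the stated sample size does not rest on the mortality contrast.

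These points limit the finding, but none of them reconciles the aim with the analysis.

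**Conclusion.** The point holds as a contradiction between the second aim and the analysis described for it. The aim calls for condition-matched people without ICU care, and the described controls are general-population controls matched on age and sex. The planned Cox model does not close the gap, because its condition and severity covariates are described for ICU patients only. As written, the study can estimate excess mortality from illness and ICU care combined, and the promised separate effect of ICU care is not supported.

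The contradiction rests on the text alone. The argument about the model rests on one reading, that ONS controls carry no APACHE II value and no acute-illness category, which is what the article describes. The apparent hazard ratios of 1.2 to 1.9 are illustrative: they rest wholly on assumed prevalences and hazard ratios and do not estimate the bias in this study.

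**What to change.** Three linked changes to the text:

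1. Restate the second aim, and the conclusion drawn from it, as the excess mortality of ICU survivors over the age- and sex-matched general population, reflecting illness and ICU care combined. Remove the reference to condition matching.
2. Confine APACHE II predicted mortality and the 12 diagnostic categories to a prognostic model fitted within ICU survivors.
3. Remove the ICU-care effect from the results table. Report the patient-versus-control contrast separately, under the wording in item 1.

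These changes need no extra patients and no new data. The cost is a narrower claim, close to what the plan already expects to find.

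The alternative is to keep the condition-matched aim and name a control source that records both diagnosis and ICU exposure, with matching on condition and exclusion of people who have had ICU care. That is a substantially larger data request than the one described to ONS and should be costed before it is chosen.

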## Methods/Design

This is a multi-centre, longitudinal study.

### Ethics Approval

Ethics approval was granted from Oxfordshire Research Ethics Committee B (Ref:06/Q1605/17).

### Participants

Participants meeting the inclusion criteria will be recruited from 20–30 intensive care units in the UK.

### Inclusion criteria

To be eligible for enrolment in the ICON study, participants must have experienced at least 24 hours of level three dependency care (ICU) at any time during their hospital stay and who survive until the time of hospital discharge.

### Exclusion criteria

Patients will be excluded if they are: aged under 16 years; unable to complete questionnaires; foreign nationals; in residential care; unable or unwilling to consent; or if their life status cannot be traced (i.e. have no GP or NHS numbers).

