### Procedure

Lists of patients meeting the study inclusion criteria will be sent from the participating hospitals to the trial office, which then submits this list to the Office of National Statistics (ONS). The ONS then performs two checks on the data. The first check cleans the list to maximise the identification of individual patients on the ONS databases; the second check identifies the patients that have died since hospital discharge. From the list of surviving patients generated by the ONS, contact with the patient's GP is made to act as a further check to confirm that the patient is still alive. Adopting this approach will hopefully prevent a questionnaire pack being mailed to a deceased patient and unnecessary distress being caused to their relative.

The three-month mailing pack consists of an introductory letter to the study, a patient information sheet, consent form, questionnaire set and a FREEPOST envelope. If the questionnaire pack is not returned, a reminder mailing is posted four weeks later. Once a patient is enrolled into the study, they will receive further study packs at 12 and 24 months post ICU discharge as long as they are not subsequently identified as deceased by the pre-mailing ONS check. The 12 and 24 month mailing packs comprise a reminder letter of the study, the relevant questionnaire packs and a FREEPOST envelope.

Again, if the patient has not returned either pack 4 weeks after the initial mailing, a second pack will be sent. If the questionnaire packs are not returned after the second mailing, no further attempts will be made to contact the patient.

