### Data collection

Participating ICUs will submit monthly lists of patient names, hospital numbers, CMP numbers, dates of birth, addresses, and both hospital/ICU admission and discharge dates to the trial office. Just prior to a patient reaching the 3 months post-ICU discharge date, the trial office will contact the patient's GP to check the patient status on the relevant patient administration system and ensure eligibility for trial entry. Once it is confirmed that the patient was successfully discharged from hospital and is still alive, a three month study pack is mailed. ICNARC (Intensive Care National Research and Education Centre) will download clinical data to the study office quarterly. Unique database numbers will link these data with the ICON database, allowing record linkage studies with ICNARC. The study office will also snapshot each participating ICU every six months for staff and unit demographics.

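### Residential care and inability to complete questionnaires are undated exclusions judged after the ICU stay, so survivors newly disabled by their illness can be removed from a sample described as representative

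*Protocol article*

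**What the plan says.** - **Exclusion criteria.** The list includes "unable to complete questionnaires; foreign nationals; in residential care". No reference date is attached, and a status that predates the ICU stay is not separated from one that arose after it.
- **Inclusion criteria.** Beyond a day of level three care, the patient need only be alive at hospital discharge.
- **Data collection.** "Just prior to a patient reaching the 3 months post-ICU discharge date, the trial office will contact the patient's GP". One stated purpose of this contact is to "ensure eligibility for trial entry". It is the only eligibility check described.
- **Procedure.** "The three-month mailing pack consists of an introductory letter to the study, a patient information sheet, consent form, questionnaire set and a FREEPOST envelope". Consent is therefore sought at the first outcome time point.
- **Abstract, Methods/Design.** "Patients will be recruited prior to hospital discharge from 20–30 ICUs in the UK". This conflicts with the two sections above.
- **Aims and objectives.** The target is a "large, representative sample of survivors of adult, general ICU care in the UK".
- **Outcome assessments.** Functional status and health-related quality of life are listed as outcomes. The EQ-5D dimensions include mobility, self-care and usual activities.
- **Planned analyses.** The quality-of-life and psychological results will be largely descriptive tables.

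**The concern.** After critical illness, moving into a care home or losing the ability to fill in a form can be a severe form of the outcomes this study measures. If such a change leads to exclusion, the patient is removed partly because of the outcome. The remaining survivors are then in better functional health than survivors as a whole.

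The study's purpose is descriptive: prevalence of morbidity, quality of life, and QALYs built from survival and EQ-5D data to inform economic modelling. Who is in the denominator is therefore central. Recruiting more patients narrows the confidence interval but leaves this bias unchanged.

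If the exclusion is applied at the 3-month contact, the same event is also handled differently according to timing. A survivor who enters care in month 2 is never studied. One who enters care in month 4 stays in, because the Procedure section stops later mailings to enrolled patients only for death.

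**Working it through.** **1. When is the status judged?** The text allows two readings.

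| Reading | Source | Time of judgement | Can the status result from the illness? |
|---|---|---|---|
| Entry at the GP contact and 3-month pack | Data collection; Procedure | About 3 months after ICU discharge | Yes |
| Recruitment before hospital discharge | Abstract | After the ICU stay, before leaving hospital | Yes, for example a planned discharge to a care home |

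The problem is present on both readings. It is larger on the first, which leaves more time for new placements.

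**2. What does it overlap with?** Self-care, mobility and usual activities are EQ-5D dimensions, and functional status is a listed outcome. The overlap is direct for function and physical quality of life. No such overlap with HADS or PCL-C scores is stated.

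**3. Size (illustration only).** The Sample size section gives a target of at least 1000 survivors returning all questionnaires. It states no precision, power or effect size, so there is no plan figure to reproduce.

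Let *p* be the prevalence among included patients, *f* the excluded share of survivors, and *m* the ratio of prevalence in excluded to included patients.

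- True prevalence = (1 − f)·p + f·m·p
- Understatement = f·p·(m − 1)
- 95% half-width at n = 1000 = 1.96·√(p(1 − p)/1000)

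The values 10%, 30% and 43% lie within or at the ends of the literature ranges in the Background (anxiety 12-43%, depression 10-30%). They only set a scale, since the document gives no prevalence for functional impairment. The values of *f* and *m* are assumptions.

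Examples at p = 30%: f = 5%, m = 1.5 gives 0.05 × 30 × 0.5 = 0.75 points; f = 20%, m = 2 gives 0.20 × 30 × 1 = 6.0 points.

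| p | Half-width (points) | f = 5%, m = 1.5 to 2 | f = 10%, m = 1.5 to 2 | f = 20%, m = 1.5 to 2 |
|---|---|---|---|---|
| 10% | 1.9 | 0.25-0.5 | 0.5-1.0 | 1.0-2.0 |
| 30% | 2.8 | 0.75-1.5 | 1.5-3.0 | 3.0-6.0 |
| 43% | 3.1 | 1.1-2.2 | 2.2-4.3 | 4.3-8.6 |

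**4. When does bias equal sampling error?** Set f = half-width / (p·(m − 1)). At p = 30%, m = 2 gives 2.84/30 = 9.5% excluded, and m = 1.5 gives 2.84/15 = 18.9%.

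**5. Can the direction reverse?** Yes, if excluded patients have the lower prevalence. With m = 0.75 and p = 30%, the study would overstate prevalence by 0.05 × 30 × 0.25 = 0.4 points at f = 5%, and by 0.20 × 30 × 0.25 = 1.5 points at f = 20%.

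**6. What if unscored survivors are simply added to the denominator?** If 20% of survivors have no scores and are counted as non-cases, a 30% prevalence becomes 0.80 × 30 = 24%. That would worsen the understatement.

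**The case against.** The strongest defence is that the text never says these two criteria are checked at 3 months. Data collection speaks of eligibility in general, and its next sentence makes mailing depend only on the patient having been discharged and being alive. Procedure describes the GP contact as a further check that the patient is alive. Hospitals submit lists of patients meeting the inclusion criteria, and the abstract puts recruitment before discharge. A reader might infer that the protocol expressly screens out care-home residents at 3 months; it does not say that. This part of the objection stands. It does not remove the concern, because the criteria are undated and either timing falls after the ICU stay.

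Secondly, some excluded patients will have been in care or unable to complete forms before admission. Leaving them out is a legitimate restriction of the population. This stands too, but the text does not separate them from the newly affected.

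Thirdly, a postal self-report survey cannot score people who cannot fill in forms. That is true, and it explains missing scores. It does not make those who remain representative, and it does not apply to a newly placed resident who could reply.

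Fourthly, recording a status for people who have not yet consented needs a legal basis, and the section on data protection says that approval is still to be sought. This is a real constraint on the remedy.

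**Conclusion.** The concern holds in a limited form. The exclusions are undated, are judged after the illness on any reading of the text, and overlap with function and physical quality of life. They conflict with the aim of a representative sample. Impairment in those domains is likely to be understated.

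The size cannot be derived from the document. At 30% prevalence it is about 1-6 points (0.75 to 6.0) if 5-20% of survivors are excluded at a prevalence ratio of 1.5-2, against a half-width of 2.8 points. The lower part of that range is within sampling error.

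Three stronger readings are not supported:

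- **That all morbidity is understated.** For anxiety, depression and PTSD symptoms nothing in the document fixes the direction, and it reverses if excluded survivors have the lower prevalence.
- **That the bias reaches 10 points.** That needs 20% excluded and a contrast such as 80% against 30%: 0.20 × (80 − 30) = 10. The document supports neither figure. At 5% excluded the same contrast gives 2.5 points.
- **That the nationality exclusion is redundant because untraceable patients are already excluded.** The protocol states no purpose for it, so no change is proposed.

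**What to change.** 1. Define residential care as residence before the index hospital admission, so that newly placed survivors are still mailed.
2. State when each exclusion is judged, and reconcile the abstract's recruitment time with Procedure and Data collection.
3. Use the existing GP contact, within the data approvals being sought, to count survivors newly in care or newly unable to complete forms. Report them as a separate status beside the questionnaire results, and do not count them as non-cases in the symptom-prevalence denominator.
4. If this is not done, restate the target population as survivors who live outside residential care and can complete questionnaires themselves, and withdraw the word representative.

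**Cost.** Items 1, 2 and 4 are wording. Item 3 adds one status field to a contact already made, and that field must be covered by the data approval. These patients will yield few or no questionnaire scores, so the gain is mainly a known count of those left out, plus scores from newly placed residents who can respond.
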